### Secondary objectives

1. To determine the associations between CVD risk factors at baseline in 15 - 18 year old youth. Investigate the relationship between specific measures within, and between participants.

### Participants

A South Lanarkshire school of low socio-economic status (SES) was selected to participate in the study. Free school meal eligibility was used to determine SES. This method has previously been validated as an accurate and valid measure of SES in children [46] and as such, allowed the researcher to objectively distinguish between low and high SES groups. Following initial discussions with the school principal and relevant teaching staff, written consent from the principal will be attained. Upon receipt, members of the research team will visit the intended participants from secondary 5 (15 - 17 years) and secondary 6 (16 - 18 years) to discuss the project. Thereafter, information sheets, participant assent forms and parental/guardian consent forms will be distributed. Only the participants who returned both the assent and consent forms will be eligible to participate in the study. Ethics approval was granted by the University of the West of Scotland Ethics committee.

### Data Analysis

A pre- and post-intervention design will be used to compare differences in measured outcomes between participants assigned to the control group and the intervention groups. Initially, baseline data will be used to perform Pearson's product moment correlation coefficients, followed by multiple regression analysis to estimate the significance of selected predictors on CVD risk factors. Statistical significance will be set at *P *= 0.05.

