### Intervention

Participants involved in the intervention will be assigned to groups A or B by a third party using computer generated sequences of random numbers. The research team and the participants will be blinded to the randomization process, and assignment to groups will only be disclosed after baseline testing. All participants will be instructed not to change their dietary or lifestyle habits other than prescribed. The secondary 5 participants will act as the control group and will be assigned to group C (*n *= 24). Participants will be encouraged to continue their regular PA patterns.

Group A (*n *= 24) will be instructed to complete a 30 seconds (s) maximal effort sprint within a 20 m distance separated by cones (see Figure 1). The start point will be located at the mid-point of the markers. Participants will be instructed to sprint from the midpoint to the first marker, turn, and then sprint 20 m in the opposite direction to the second marker. Thereafter, participants will turn and run again through the midpoint covering a total distance of 40 m. Though this protocol has been used and validated as a measure of anaerobic performance [47], in this study, participants will be instructed to sprint maximally for a period of 30 seconds. Following 30 s rest, the participants will be instructed to repeat this procedure a further 3 times. This equates to 2 minutes (mins) of maximal effort sprinting interspersed with 2 mins recovery. Participants will be requested to perform this protocol 3 times weekly. Training progression will be implemented by increasing the number of repeats from four repetitions during weeks 1 and 2, to five repetitions during weeks 3 and 4, to six repetitions during weeks 5 and 6. Finally, during week 7 participants will still perform six repetitions but interspersed by only 20 s recovery. Prior to the commencement of the training regime, participants will be given a familiarization trial of four low intensity runs under test procedures.

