#### Sample size

In order to determine sensitivity to change, sample size will be estimated using the procedures of Park and Schutz [67] for ANOVA designs that incorporate a repeated factor. For a medium effect size in the intervention groups of d = 0.50, power of .80 (suggesting an 80% probability of achieving significance at the *p *= .05 level) this is achieved with a group size of 17 participants. Effect sizes > 0.5 indicate clinically relevant changes [68]. Assuming a drop-out rate of 30%, this would require an initial recruitment of 24 participants per group. The intervention will be carried out during the lunch hour or PE lessons, on Monday, Wednesday and Friday, and for a period of 8 weeks. The interventions will be performed in the school sports hall; led initially by the research team and then by the PE teacher; and during January through May, 2009, to allow for uninterrupted use of the facilities.

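### For the randomised A versus B comparison, adjusting the post value for baseline is more precise than the pre/post difference the plan points to, and costs nothing

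*Protocol article*

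**What the plan says.** The Data Analysis section of the protocol article describes the intervention comparison in one sentence: "A pre- and post-intervention design will be used to compare differences in measured outcomes", with the control group set against the intervention groups. It names no test or model for this. The correlations and multiple regression in that section use baseline data only and serve the secondary objective. Baseline is not mentioned as a covariate for the intervention effect.

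ANOVA appears only under Sample size, where the calculation is for "ANOVA designs that incorporate a repeated factor". The inputs there are "For a medium effect size in the intervention groups of d = 0.50, power of .80" at the 5% level, and "this is achieved with a group size of 17 participants". Recruitment is raised to 24 per group for 30% drop-out.

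Under Intervention, secondary 6 pupils are "assigned to groups A or B by a third party using computer generated sequences of random numbers". The control group C is the secondary 5 year group and is not randomised. Under Measurements, all outcomes are taken pre and post in all groups. The vertical jump, 10 m sprint, 20 m shuttle test (20MSFT) and 505 agility test are also taken at the end of week 4 in the intervention group.

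**The concern.** The only between-group framework in the document is a pre/post comparison sized by a repeated-factor ANOVA. With two time points, the group-by-time interaction of that ANOVA is a two-sample test on post minus pre. A change score subtracts the whole baseline value, whatever the pre-post correlation. ANCOVA subtracts only the share of baseline that predicts the post value. Under randomisation both estimate the same A versus B effect, and ANCOVA has the smaller residual variance whenever r is below 1.

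Precision is at stake. With 17 evaluable pupils per group the trial has little to spare, and the baseline values are collected anyway. A strict two-point comparison would also leave unused the week-4 fitness values of any pupil who has no post-test.

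**Working it through.** **Inputs.** From Sample size: d = 0.50, power 0.80, 17 evaluable and 24 recruited per group, 30% drop-out. From Data Analysis: 5% level, taken as two-sided because sidedness is not stated. The pre-post correlation r is not given, so it is varied. Pre and post SDs are assumed equal and set to 1.

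**1. The plan's own figure.** Take the group-by-time interaction with 2 groups, 2 times, f = d/2 = 0.25 and an assumed r = 0.5. The noncentrality is λ = f² × N × m/(1 − r) = 0.0625 × 34 × 2/0.5 = 8.5 on 1 and 32 degrees of freedom, which gives power 80.7%. So 17 per group is reproduced. For drop-out, 17/0.7 = 24.3, and 24 × 0.7 = 16.8, so the stated 24 agrees to rounding.

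**2. Equivalence with the change score.** A change score has variance 2(1 − r). For a between-group difference δ in mean change, the squared t noncentrality is δ² × n/(2 × 2(1 − r)). With n = 17, r = 0.5 and δ = 1.0 this is 17/2 = 8.5, the same λ as in step 1. The two tests are the same test. It also follows that f = 0.25 on the interaction stands for a 1.0 SD difference in change, not 0.5 SD.

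**3. Change score against ANCOVA, A versus B.** The residual variances are 2(1 − r) and 1 − r². Their ratio is (1 − r²)/(2(1 − r)) = (1 + r)/2, so the share of information lost by the change score is (1 − r)/2. Power is from the noncentral t for a true difference of 0.5 SD, with standardised effects 0.5/√(2(1 − r)) and 0.5/√(1 − r²).

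| r | Change variance | ANCOVA variance | Information lost | Power at 17 per group, change v ANCOVA | n per group for 80%, change v ANCOVA |
|---|---|---|---|---|---|
| 0.3 | 1.40 | 0.91 | 35% | 22% v 32% | 89 v 59 |
| 0.5 | 1.00 | 0.75 | 25% | 29% v 37% | 64 v 49 |
| 0.7 | 0.60 | 0.51 | 15% | 45% v 51% | 39 v 34 |
| 0.8 | 0.40 | 0.36 | 10% | 61% v 65% | 27 v 24 |

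The loss is 50% at r = 0 and 5% at r = 0.9. A normal approximation gives slightly different values at r = 0.5 (31% v 39%; 63 v 48 per group), with the same conclusion. Charging ANCOVA one degree of freedom for the covariate moves its power at r = 0.5 only from 37.2% to 37.1%.

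**4. Week-4 values.** The planned drop-out is 0.30 × 24 = 7.2, about 7 pupils per group. ANCOVA on the post value needs that value, so by itself it recovers none of them. A model with week 4 and post as responses keeps those who leave between the two visits, but only for jump, 10 m sprint, 20MSFT and 505. How many that would be cannot be computed, because the document gives no timing of drop-out.

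**The case against.** The strongest reply is that the article does not fix the analysis. The Data Analysis sentence can be read simply as comparing outcomes between groups, and no test is named. ANOVA is the basis of the sample size only, and an analysis plan that is not shown may already specify ANCOVA. This stands as far as it goes: repeated-measures ANOVA as the analysis model is inferred. It does not remove the point, because the article gives no other between-group framework, and the method it points to is less precise than one that uses the same data.

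The second reply also stands. The quoted sentence concerns control against intervention, and group C is a different, non-randomised school year. If baselines differ, change score and ANCOVA can estimate different effects there, and efficiency does not settle the choice. The point is therefore confined to A versus B.

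Three stronger readings are tempting and not supported:
- A reader might infer that the plan loses every pupil without a post-test. The document states no completers-only rule, and inflating recruitment for drop-out says nothing about the analysis set. Plain ANCOVA would lose the same pupils.
- A reader might take a quarter as the most that can be lost. It is the value at r = 0.5; below that the loss is larger.
- A reader might infer that allocation ignores sex and must be stratified. The article does not say whether the sequence is stratified, and unstratified randomisation is valid.

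**Conclusion.** The point holds as a free improvement limited to the randomised A versus B contrast. If the analysis follows the framework of the sample size, it gives up (1 − r)/2 of the information relative to ANCOVA: 10% to 25% for r between 0.8 and 0.5, and more if r is lower. This assumes equal pre and post SDs, a two-sided 5% test and a linear relation of post to baseline, and r itself is an assumption. For a 0.5 SD difference with 17 per group and r = 0.5, the gain is from about 29% to 37% power. That is worth having, but it leaves the comparison far below 80%; the adequacy of the sample size is a separate matter. Nothing here shows the planned comparison of A with B to be invalid or biased.

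**What to change.** State that A versus B will be analysed by ANCOVA on the post value, with the baseline value of the same outcome as covariate.

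For 20MSFT, jump, 10 m sprint and 505, use a mixed model with baseline as covariate and the week-4 and post values as responses, and take the A versus B difference at post as the estimate. Pupils who leave after week 4 then still contribute.

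Treat A or B versus C separately. Say which of change score or baseline adjustment is used and why, given that C is a non-randomised year group.

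The cost is a few sentences of analysis wording. No measurement, visit or pupil is added.

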### Intervention

Participants involved in the intervention will be assigned to groups A or B by a third party using computer generated sequences of random numbers. The research team and the participants will be blinded to the randomization process, and assignment to groups will only be disclosed after baseline testing. All participants will be instructed not to change their dietary or lifestyle habits other than prescribed. The secondary 5 participants will act as the control group and will be assigned to group C (*n *= 24). Participants will be encouraged to continue their regular PA patterns.

Group A (*n *= 24) will be instructed to complete a 30 seconds (s) maximal effort sprint within a 20 m distance separated by cones (see Figure 1). The start point will be located at the mid-point of the markers. Participants will be instructed to sprint from the midpoint to the first marker, turn, and then sprint 20 m in the opposite direction to the second marker. Thereafter, participants will turn and run again through the midpoint covering a total distance of 40 m. Though this protocol has been used and validated as a measure of anaerobic performance [47], in this study, participants will be instructed to sprint maximally for a period of 30 seconds. Following 30 s rest, the participants will be instructed to repeat this procedure a further 3 times. This equates to 2 minutes (mins) of maximal effort sprinting interspersed with 2 mins recovery. Participants will be requested to perform this protocol 3 times weekly. Training progression will be implemented by increasing the number of repeats from four repetitions during weeks 1 and 2, to five repetitions during weeks 3 and 4, to six repetitions during weeks 5 and 6. Finally, during week 7 participants will still perform six repetitions but interspersed by only 20 s recovery. Prior to the commencement of the training regime, participants will be given a familiarization trial of four low intensity runs under test procedures.

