## Abstract

**Background:**

Cardiovascular disease (CVD) is the main cause of mortality throughout the world. With accumulating evidence suggesting that CVD has its origins in childhood, it is unsurprising that research into obesity prevalence within school aged youth is burgeoning.

Within this study our primary objective will be to examine whether high intensity interval training (HIT) improves the CVD risk profile of secondary school aged adolescents. Our secondary objective will be to identify the prevalence of CVD risk factors and examine factors associated with these in adolescents aged 15 - 18 years.

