**Method/Design:**

A South Lanarkshire school of low socioeconomic status (SES) was selected to participate in the study intervention. Participants from secondary 5 (15 - 17 years) and 6 (16 - 18 years) will be recruited for this study. Participants from secondary 6 will be randomly assigned to Group A (HIT) or Group B (moderate-vigorous) and will perform each protocol three times weekly. The secondary 5 participants will act as the control group. Data collection will take place during the Physical Education (PE) lessons and on school premises and will include: anthropometrical variables (height, weight, waist and hip circumferences, skinfold thickness at two sites), physiological responses (blood pressure, aerobic fitness, heart rate (HR) response, vertical jump performance, 10-metre (m) sprint, 50-m sprint and 505-agility test), diet (self-reported seven-day food diary), physical activity (Physical Activity Questionnaire for Adolescents (PAQ-A)) and blood tests (fasting glucose, insulin, total cholesterol (TC), high-density lipoprotein (HDL), high-sensitivity C-reactive protein (hs-CRP), fibrinogen (Fg), interleukin-6 (IL-6), adiponectin (high molecular weight), triglyceride and plasminogen activator inhibitor-1 (PAI-1). An environmental audit of the secondary school and the health related quality of life (HRQOL) of the participants will also be measured. Finally, all exercise sessions will be video recorded and rate of perceived exertion (RPE) and mood states will also be taken after each exercise session.

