#### Questionnaires

All participants will be instructed to complete the physical activity questionnaire for adolescents (PAQ-A). This validated questionnaire has been used in previous research [60] with participants instructed to recall their PA behavior from the previous 7 days. From previous experience we envisage that completion of the questionnaire will take no longer than 30 minutes and thus can be completed during scheduled class time. Sexual maturation status will be determined through the use of a self-reported questionnaire [61]. Participants will be asked to indicate their current stage of development regarding their pubic hair and genital development. Health related quality of life (HRQOL) will be measured through the use of the paediatric quality of life inventory (PedsQL™) for both the participant and their parent/guardian [62]. The PedsQL™ has been shown to be a valid and reliable instrument specifically developed for use with children and adolescents [63]. The brief one page instrument has 23 questions and covers four dimensions: physical functioning, emotional functioning, social functioning and school functioning.

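### The control group is a different school year and is not randomised, so every comparison with control is confounded with year group; HIT versus moderate exercise (A versus B) is not affected

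*Protocol article*

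**What the plan says.** The Abstract describes recruitment from two school years: "Participants from secondary 5 (15 - 17 years) and 6 (16 - 18 years) will be recruited for this study". It then limits randomisation to the older one: "Participants from secondary 6 will be randomly assigned to Group A (HIT) or Group B (moderate-vigorous" exercise). The Intervention section agrees: "Participants involved in the intervention will be assigned to groups A or B by a third party using computer generated sequences of random numbers". Group C does not enter that allocation: "The secondary 5 participants will act as the control group and will be assigned to group C", with 24 pupils.

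The Data Analysis section gives one between-group comparison, a pre-post design to "compare differences in measured outcomes between participants assigned to the control group and the intervention groups". It serves the aim set out in the Abstract: "our primary objective will be to examine whether high intensity interval training (HIT) improves the CVD risk profile of secondary school aged adolescents".

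Two further items bear on adjustment. Under Questionnaires, "Sexual maturation status will be determined through the use of a self-reported questionnaire", but no role for it in the group comparison is stated. The regression in the Data Analysis section starts from a different place: "baseline data will be used to perform Pearson's product moment correlation coefficients, followed by multiple regression analysis". It looks for predictors of CVD risk factors at baseline and does not adjust the comparison between groups.

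**The concern.** Every control pupil is in secondary 5 and every trained pupil is in secondary 6. A difference between control and trained pupils in how outcomes change could come from training, from belonging to a different school year, or from both, and the data cannot say which. Outcomes such as BMI, skinfolds, shuttle-run performance, sprint and jump can plausibly change at different rates in adolescents of different age or maturity.

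At stake is the main question. Whether HIT improves the risk profile, as opposed to doing nothing extra, can only be read from a contrast with group C, and that contrast lacks the protection of randomisation. The Discussion section aims to determine whether HIT can confer CVD protection, which is a causal aim.

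**Working it through.** **Inputs from the protocol article.** Groups of 24 (Intervention); 17 completers per group, 30% drop-out and 24 recruited (Sample size); significance level 0.05 (Data Analysis); secondary 5 aged 15–17 and secondary 6 aged 16–18 (Abstract, Participants).

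**The plan's own figures.** 17 / (1 − 0.30) = 24.3, which rounds up to 25 against the stated 24; conversely 24 × 0.70 = 16.8. The drop-out step is right to within one pupil. The 17 itself depends on a pre-post correlation that the article does not give, so it can be neither confirmed nor refuted. This point does not rest on it.

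**Step 1: what can be separated.** Let T = 1 for a pupil in A or B and 0 in C. Let Y = 1 for secondary 6 and 0 for secondary 5.

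| Group | Planned n | T | Y |
|---|---|---|---|
| A | 24 | 1 | 1 |
| B | 24 | 1 | 1 |
| C | 24 | 0 | 0 |

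T = Y for all 72 pupils. A model containing both terms has two identical columns, so a year-group effect cannot be estimated apart from the control-versus-intervention effect.

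**Step 2: what each contrast estimates.** Write the mean change from pre to post as m + τ_A + b in A, m + τ_B + b in B and m in C. Here τ is the training effect and b is the difference in change between the years that is unrelated to training.

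- A versus C estimates τ_A + b.
- B versus C estimates τ_B + b.
- A versus B estimates τ_A − τ_B; b cancels.

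A constant difference in level between the years drops out when change is analysed. Only a difference in change remains as b.

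**Step 3: size, on an assumed b.** The article gives no value for b. Express it in SDs of the change score and set τ_A = 0. The two-sample t statistic for A versus C then follows a non-central t distribution with 2n − 2 degrees of freedom and non-centrality b × √(n/2). The probability of a significant result is P(|t| > c), where c is the two-sided 5% critical value. The article does not say whether tests are two-sided; two-sided is assumed.

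- n = 17: df = 32, c = 2.037, √(17/2) = 2.915.
- n = 24: df = 46, c = 2.013, √(24/2) = 3.464.

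| Assumed b (SD of change) | Non-centrality, n = 17 | P(significant), n = 17 | Non-centrality, n = 24 | P(significant), n = 24 |
|---|---|---|---|---|
| 0 | 0 | 0.050 | 0 | 0.050 |
| 0.1 | 0.292 | 0.059 | 0.346 | 0.063 |
| 0.25 | 0.729 | 0.109 | 0.866 | 0.136 |
| 0.5 | 1.458 | 0.293 | 1.732 | 0.396 |

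Recruiting more pupils does not help: at 48 per group and b = 0.25 the probability is 0.228. A b that opposes the training effect would hide it instead.

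**Step 4: what adjustment can do.** The age ranges share 16–17 years, so some pupils in the two years are comparable in age and probably in maturation. These covariates can absorb part of b. By Step 1, whatever belongs to the school year itself stays in the contrast.

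**The case against.** The strongest reply has four parts.

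- **The control is openly described.** Nothing is mislabelled as randomised, the study calls itself a pilot, and the Abstract's closing claim is hedged. This stands as a defence of the reporting. It does not make the comparison unconfounded.
- **An article's short Data Analysis section is not a full analysis plan.** Covariates and the list of contrasts are often left to one. The plural reference to intervention groups, the repeated-factor ANOVA under Sample size and the stated interest in exercise intensity all leave room for A versus B. This is a fair limit: the absence of covariates is not itself the fault, and A versus B is not excluded. Allocation by school year, however, is fixed in this document, and a later plan cannot undo it.
- **The bias may be small.** Over 7 weeks (8 in the Sample size section), adjacent and overlapping year groups may change almost alike. That is possible: at 0.1 SD the error rate is close to nominal. The protocol offers nothing to show which part of the range applies.
- **Randomising across years has costs.** Controls in the same year as trained pupils invite contamination, and measurements are tied to normal PE lessons. This stands, and is why that option is not the main recommendation.

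A reader might go further and infer that the whole HIT evaluation is confounded, that age and maturation are perfectly aligned with treatment, or that the two years have different PE timetables. The documents do not support these readings. A versus B is randomised within one year, the age ranges overlap, and no section describes a timetable difference.

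**Conclusion.** The concern holds for comparisons with group C and only for those. The named control-versus-intervention comparison is non-randomised and completely confounded with school year, and this follows from the allocation alone without any assumption. Its numerical effect does rest on assumptions: a year-group difference in change of 0.1 to 0.5 SD, no training effect, and a two-sided t-test. Across that range the false-positive rate runs from about 6% to 29% at 17 completers per group, and from about 6% to 40% at 24. These figures illustrate how sensitive the test is; they do not estimate the bias in this trial. A versus B remains a valid randomised contrast, but it answers a narrower question: HIT against moderate exercise, not HIT against no training.

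**What to change.** In the Data Analysis section:

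1. Name A versus B as the confirmatory, randomised comparison.
2. Report A versus C and B versus C as non-randomised estimates, adjusted for baseline value, age, sex and the maturation stage already collected. State that year group cannot be adjusted for.
3. Make no causal claim from the comparisons with C, and align the stated aims in the Abstract and Discussion sections with this.

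**Cost.** No new visits or tests. Age and sex are assumed to be on record from enrolment. The claim against no training becomes weaker. A versus B may also have little power: if the two differed by 0.5 SD of change, the same t calculation gives 29% power at 17 per group and 40% at 24. The protocol's d = 0.50 is not tied to that scale, so this too is an illustration.

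**Option, if the school can accommodate it.** Randomise to A, B or C within each school year, using the existing third party and the same total of 72. This removes the confounding, but it is a redesign, with mixed-year timetabling and a risk of contamination between pupils in the same year.
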